**Over night pulse oximetry and day 3 assessment**

In order to ascertain whether the prescribed oxygen supplementation effectively prevents hypoxia pulse oximetry will be performed over night on night two while the patient is receiving oxygen or control treatment. We will also be able to quantify the time the patients spend with an oxygen saturation above the normal range. This is necessary to fine tune the dosage schedule for the planned outcome study.

The day 3 assessment (Assessment Form 1) will document compliance with the trial treatment, relevant aspects of the patient's past medical history, and the stroke type (Oxfordshire Community Project Stroke Classification), and confirm completion of the over night pulse oximetry. If incomplete, pulse oximetry will be repeated on night 3 of treatment.

**Week 1 assessment**

The week 1 assessment (Assessment form 2) is designed to screen for potential adverse effects of oxygen and includes indicators of infection, stress (tachycardia and hypertension), behaviour disturbance, cognitive function, and neurological deterioration. If the patient is well enough to cooperate the researcher will discuss the 6 month assessment and find out who the preferred contact (s) for mailing of the questionnaire.

**Month 3 assessment**

The month 3 assessment (Assessment Form 3) documents the length of stay in hospital, and discharge destination. The discharge address and the contact details of the GP are recorded in preparation for the 6 month follow-up. It will be completed at 3 months, or before where appropriate. It will be completed using information from the HISS/CHIPS system and patient notes.

**Month 6 assessment**

This assessment (Assessment Form 4) will provide the main outcome (death and disability at 6 months) data for testing the trial hypothesis of the planned larger study. It consists of a questionnaire which will be sent to the patient's preferred contact address (if known) or the discharge address. Outcomes will be assessed using well validated scales (Rankin[[39]](#endnote-40) [[40]](#endnote-41), 3-point Barthel,[[41]](#endnote-42) Euroquol,[[42]](#endnote-43) [[43]](#endnote-44) The Nottingham Extended Activities of Daily Living Index[[44]](#endnote-45) [[45]](#endnote-46)). As in other large studies looking at outcome after acute stroke (e.g. the IST-3 study of thrombolysis for acute stroke currently in progress at out hospital), we will first ascertain whether that patient is still alive (via the hospital computer system and/ or the GP) and then contact the patient by post or by telephone.

This pilot trial aims to assess the likelihood of patients or carers completing the questionnaire. If the relevant information cannot be collected via mail or by phone we will consult patient records and the GP to ascertain outcome data. If a significant proportion of questionnaires is not returned or incomplete we will redesign the questionnaire for the main study or consider alternative methods of ascertaining the main outcomes.

For this pilot we will also collect information on length of stay, readmissions and discharge destination. These data will be gathered using the hospital HISS/CHIPS system (Assessment Form 5). These will allow us to provide basic health economic data. The date and cause of death will be recorded on Assessment Form 6 and contact details for follow up on Assessment Form 7.

**Research Staff**

There will be a full time PhD student (self funding) and a part time research nurse (funded by Geriatric Medicine Research Funds) working on the project.

To allow for 24 hour inclusion of patients by A&E or MAU staff the randomisation procedures are kept very simple. The Trust admits about 2-3 stroke patients per day, and most of those would be randomised by the research team. A&E and MAU staff will only be asked to randomise patients if the unit managers agree with the trial, and if the staff involved are not too busy. While it is expected that the majority of patients will be recruited by the research team, it is considered important for this pilot study, since recruitment by other staff than the core research team will be required for the larger multicentre trial, and any problems with this are likely to become obvious in the pilot phase.

**Main outcomes**

Comparisons will be made between the treatment and control group to determine:

1. Effect size:

- Death and disability (Rankin >3) at 6 months
- Scandinavian Stroke Scale week 1
- Mortality up to 6 months
- Rankin Score at 6 months
- Nottingham EADL score at 6 months

2. Potential Side effects of the study treatment

- Rate of infections (pyrexia or antibiotic treatment at week 1)
- Agitation (sedative or antipsychotic medication at week 1)
- Physiological indicators of stress (tachycardia, hypertension)

3. To assess the feasibility of the study protocol we will examine

- Protocol violations
- Recruitment rate
- The relation between the number of recruited and excluded patients
- The percentage of completed 6-month questionnaires

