**Randomisation and initial assessment**

This assessment is limited to the minimum baseline clinical data required for randomisation and clinical assessment (See Randomisation Form) and incorporates validated tools (Glasgow Coma Scale,[[34]](#endnote-35) [[35]](#endnote-36) Prognostic Factors,[[36]](#endnote-37) and Scandinavian Stroke Scale[[37]](#endnote-38)). This form may be filled in by medial staff in the admissions unit after appropriate training allowing 24/7 recruitment. It is thus kept as short as possible to avoid the randomisation process interfering with clinical care. Any relevant background details which can be retrieved from the notes will be collected by the researcher at the day 3 assessment.

Patients will be randomised by telephone by simple randomisation. We considered using minimisation to balance prognostic characteristics between the treatment and control groups, but decided against this for the pilot since there is a significant chance of guessing trial allocation with this method with a single centre trial.

We are, however, considering treatment allocation by minimisation using well-established factors predictive of stroke outcome (living alone before the stroke, pre stroke functional independence, normal verbal response, ability to lift the affected arm against gravity and ability to walk unaided)[[38]](#endnote-39) and a measure of hypoxia (block 1: baseline saturation 92%, block 2: baseline saturation 93-94%, block 3 baseline saturation 95%) for the planned multicentre trial, and have therefore included the minimisation criteria on the randomisation form.

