**Stroke Oxygen Study**

**Week 1 (Assessment form 2 a)**

Name Randomisation no

Date of death (if applicable)

Please complete the Notification of Death Form if the patient is deceased.

| Antibiotics prescribed since admission | YES | NO |
| --- | --- | --- |
| Continuous oxygen prescribed outside protocol for clinical indications | YES | NO |
| Sedatives or antipsychotic drugs prescribed since admission | YES | NO |
| Highest temperature during week 1 |  |  |
| **The highest heart rate during the 3 days of trial treatment** |  |  |
| **The highest systolic blood pressure during the 3 days of trial treatment** |  |  |
| **The highest diastolic blood pressure during the 3 days of trial treatment** |  |  |
| Highest temperature during week 1 |  |  |

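### Heart rate, blood pressure and temperature feed the side-effect outcomes but are not recorded before randomisation, so these comparisons cannot be adjusted for entry values and lose precision

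*Protocol*

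**What the plan says.** **Outcomes.** Under potential side effects, the Main outcomes section lists "Rate of infections (pyrexia or antibiotic treatment at week 1") and "Physiological indicators of stress (tachycardia, hypertension"). It gives no threshold and does not say that an abnormality must be new.

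**What is recorded after randomisation.** The Week 1 form (Assessment form 2a) asks for "The highest heart rate during the 3 days of trial treatment", "The highest systolic blood pressure during the 3 days of trial treatment" (with a matching line for diastolic pressure) and "Highest temperature during week 1". Each is a single numeric maximum.

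**What is recorded at entry.** The Randomisation Form holds the Glasgow Coma Scale, five prognostic factors and oxygen saturation. The Baseline Neurological Assessment holds the Scandinavian Stroke Scale only. The Day 3 form (Assessment form 1) adds medical history, stroke class and overnight oximetry. Its one heart rate is a nocturnal mean from night 2 (or night 3 if repeated), when trial treatment is under way.

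**Retrieval from notes.** The section on randomisation and initial assessment adds that "Any relevant background details which can be retrieved from the notes will be collected by the researcher at the day 3 assessment". The Day 3 form has no field for vital signs before randomisation.

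**Analysis.** The Statistical analysis section plans to compare the groups both at baseline and after treatment, with parametric or non-parametric tests.

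**The concern.** Assessing side effects is one of the pilot's four main objectives. Some patients may already be hypertensive, tachycardic or febrile when they enter the trial. If only maxima after randomisation are kept, those whose abnormality persists look the same as those in whom it is new. The planned baseline comparison cannot be made for these variables. Entry values probably explain part of the variation in the later maxima, and that part stays in the error term. At stake is how well the pilot can detect or rule out a side effect, and whether its forms are fit to carry into the larger trial. By contrast, the Scandinavian Stroke Scale is recorded at both baseline and week 1.

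**Working it through.** The protocol states no figure for the side-effect outcomes, so there is none to reproduce. Its sample size statement concerns Rankin, Nottingham EADL and EuroQuol only.

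**Inputs from the protocol:** 150 per arm, two-sided 5% level, simple randomisation.

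**Inputs assumed, because the protocol gives none:** an effect of 0.3 SD on a recorded maximum; correlation *r* between entry value and maximum of 0.4 to 0.6; for a yes/no analysis, the share *q* abnormal at entry and the event rates shown below.

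**1. Continuous analysis.** Power = Φ(d/√(1 − r²) × √(150/2) − 1.96).

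| r | SD factor √(1 − r²) | effective d | d × √75 | power |
|---|---|---|---|---|
| 0 (unadjusted) | 1.000 | 0.300 | 2.598 | 74% |
| 0.4 | 0.917 | 0.327 | 2.835 | 81% |
| 0.6 | 0.800 | 0.375 | 3.248 | 90% |

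Adjustment removes r² of the variance, which is 16% to 36%.

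**2. Chance imbalance.** If 30% are abnormal at entry, the difference in that share between arms has a 95% range of ±1.96 × √(2 × 0.3 × 0.7/150) = ±10.4 percentage points. Without entry data, an imbalance of this size could be neither seen nor adjusted for.

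**3. Yes/no analysis, every entry abnormality persisting.** Event rate = q + (1 − q) × p, with p the rate of new abnormality, here 30% v 45%. Power is for a two-proportion test. The last column counts only patients normal at entry, so 150 × (1 − q) per arm.

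| q | rates, everyone counted | difference | power, everyone | power, normal at entry only |
|---|---|---|---|---|
| 20% | 44% v 56% | 12 points | 55% | 67% |
| 30% | 51% v 61.5% | 10.5 points | 45% | 61% |
| 60% | 72% v 78% | 6 points | 22% | 40% |

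With new abnormality in 15% v 30% and q = 30%, the rates are 40.5% v 51.0%, and power is 45% against 74%.

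**4. Yes/no analysis, entry abnormalities persisting only in part and oxygen acting on these patients too.** Take 60% v 75% among those abnormal at entry and 30% v 45% among the rest.

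- q = 30%: control 0.3 × 0.60 + 0.7 × 0.30 = 39%; oxygen 0.3 × 0.75 + 0.7 × 0.45 = 54%. The difference stays at 15 points. Power is 74% with everyone counted, against 61% in those normal at entry.
- q = 60%: 48% v 63%, again 15 points. Power is 75% against 40%.

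Steps 3 and 4 point in opposite directions, and the protocol offers nothing to choose between them. Dilution is therefore possible but not established, and restricting to patients normal at entry can cost power. The gain from adjustment in step 1 needs only that entry and later values are correlated.

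**The case against.** A reader might infer that anyone abnormal at entry is bound to be scored as having a side effect, so that the comparison is distorted. The protocol does not support that. The heart rate and blood pressure window is the three days of trial treatment, and the Summary of the study dates week 1 from enrolment, so an entry abnormality counts only if it persists or recurs. Allocation is random, so whatever persists is expected equally in both arms. The form records numbers, and maxima compared as numbers are not misclassified; cut-offs and new-onset rules may also sit in a statistical analysis plan that is not at hand. All of this stands, and it limits the point to precision and interpretation.

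It can also be said that this is a pilot with no power claim for side effects, that its side-effect objective does not name tachycardia or hypertension among its examples, that the entry form is deliberately short, and that charted values could be retrieved later. These arguments lower the priority. They do not remove the gap: the list of main outcomes does name both indicators, an analysis plan cannot adjust for values that no form collects, and the short form is the admitting doctor's, whereas the researcher already goes to the notes on day 3. It would be too strong to call the loss irrecoverable, but later recovery would depend on finding old charts.

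**Conclusion.** The point holds as a modest one. Three side-effect outcomes rest on maxima after randomisation with no entry value on any form, so the planned baseline comparison and any baseline adjustment are not possible for them, and new abnormalities cannot be separated from persisting ones. The between-arm comparison remains unbiased. Under the assumed 0.3 SD effect and correlation of 0.4 to 0.6, recording entry values lifts power from 74% to between 81% and 90%. For a yes/no analysis the loss ranges from none to substantial, depending on entry prevalence, persistence and where oxygen acts, none of which the protocol gives. Severity: consider. It is a cheap gain in precision, not the correction of a bias.

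**What to change.** Add four fields to the Day 3 form: the last charted temperature, heart rate, and systolic and diastolic blood pressure before randomisation. The researcher who already reviews the notes copies them from the observation chart.

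State in the analysis section that the recorded maxima will be compared between arms as continuous values, in all randomised patients, with adjustment for the corresponding entry value. Report new-onset tachycardia, hypertension and pyrexia only as a secondary description.

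The cost is four values per patient to abstract, some of which may be missing from the chart. Nothing is added for the admitting doctor, and no treatment or procedure changes. The entry values do not settle the antibiotic half of the infection outcome, which the Week 1 form words as "Antibiotics prescribed since admission" and which can therefore include prescriptions made before randomisation.

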**DATA ANALYSIS**

**Statistical analysis**

The main comparisons will be made between the control group and the treatment group.

The main analysis will be intention to treat, but a subgroup analysis excluding protocol violators will also be performed. Appropriate parametric and non parametric tests will be used to compare the groups at baseline and after treatment.

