**Study size**

This is a pilot study and thus no formal study size calculation was undertaken since no estimate of effect size is available and the study is to be used to determine this as well as the feasibility of the planned multicentre study.

We plan to recruit 150 patients in each of the 2 trial arms. This would enable in the full sample detection of a small to medium effect size (0.4 SD of the main outcomes (Rankin, Nottingham EADL and EuroQuol) with 90% power and with a 5% two sided significance level. The study size was determined considering the following factors:

Ronning et al included almost 600 patients in their study of routine oxygen supplementation and did not find an overall difference on functional outcome at one year. There was a trend towards a better result with oxygen treatment in the 240 subjects with severe stroke, although this finding was not backed up by the use of a suitable test for heterogeneity. Our protocol may be more likely to show benefits because oxygen is given for longer, and titrated according to baseline oxygen saturation.[[46]](#endnote-47) However, given the data of the above study it is likely that any observed effect is small. This pilot study will provide us with data to inform a study size calculation.

Over the last year we performed a small study of the effects of oxygen supplementation for 24 hours within 3 days of admission on oxygen saturation. It showed a significant improvement of oxygen saturation in the treated group, but the study was not powered to look at functional outcomes. It took 6 months to recruit 50 patients for this study.[[47]](#endnote-48) It is therefore likely that we will be able to recruit 300 patients over three years.

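### The stated analysis is group tests at baseline and after treatment, with no planned adjustment for the recorded stroke severity and prognostic factors, although randomisation is simple and the estimate will size the main trial

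*Protocol*

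**What the plan says.** Protocol, Statistical analysis: the main analysis is by intention to treat, with a second analysis that leaves out protocol violators. The method is given in one sentence: "Appropriate parametric and non parametric tests will be used to compare the groups at baseline and after treatment". No covariate or model is named.

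Protocol, Randomisation and initial assessment: "Patients will be randomised by telephone by simple randomisation". Balancing by design was weighed and rejected: "We considered using minimisation to balance prognostic characteristics between the treatment and control groups, but decided against this for the pilot". The reason given is that allocation could be guessed in a single centre. The same section describes living alone, pre-stroke independence, verbal response, arm lift and walking as "well-established factors predictive of stroke outcome". It explains their presence on the form by the later multicentre trial: the authors "have therefore included the minimisation criteria on the randomisation form".

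Step 3 of the Randomisation Form records these five factors and oxygen saturation. The Baseline Neurological Assessment records a full SSS at admission. Under Main outcomes, the SSS at week 1 is also an outcome.

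Protocol, Study size: "We plan to recruit 150 patients in each of the 2 trial arms", said to allow detection of a "small to medium effect size (0.4 SD of the main outcomes" and so on, "with 90% power and with a 5% two sided significance level". The same section expects any effect to be small. The main objectives say that the 6-month differences between the groups will feed the sample size calculation for the multicentre trial.

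**The concern.** The Protocol identifies the variables it believes predict outcome, collects them on everyone, decides not to balance on them, and then gives them no role in the treatment comparison. The sentence on method applies one set of tests both at baseline and after treatment. A test on a baseline variable is a plain two-group test, so the natural reading is that the outcome comparison is one too.

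Two things are at stake. The first is precision: variation in outcome that baseline severity could explain stays in the error term. The second is the particular sample obtained: if one arm happens to start with milder strokes, that difference passes into the estimated effect. Both matter more here than in a trial that ends with its own p-value, because the estimate becomes a planning input for the next trial.

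The baseline tests do not help. Under simple randomisation any baseline difference is due to chance, so a significance test on it answers no useful question.

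**Working it through.** **Inputs.** From Study size: 150 per arm, 0.4 SD, two-sided 5%, 90% power. The share of outcome variance explained by baseline covariates, R², is not in the Protocol. It is taken as 0.10 to 0.50 by assumption. Arms of exactly 150 are assumed throughout.

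**The plan's own figure.** For two means in SD units, n per arm = 2(1.960 + 1.282)²/0.4² = 132 (133 by t test). With 150 per arm the standard error (SE) of the difference is √(2/150) = 0.1155 SD, and power for 0.4 SD is Φ(0.4/0.1155 − 1.960) = 93.4%. The effect detectable with 90% power is 3.242 × 0.1155 = 0.374 SD, which rounds to the stated 0.4. The stated power is therefore slightly conservative, and that is not part of this point.

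**Gain from adjustment, continuous outcomes.** The residual SD becomes √(1 − R²). The equivalent unadjusted n is 150/(1 − R²), and the detectable effect is 0.374 × √(1 − R²).

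| R² (assumed) | Equivalent n per arm | Detectable at 90% (SD) | Power for 0.4 SD | Power for 0.3 SD |
|---|---|---|---|---|
| 0 (unadjusted) | 150 | 0.374 | 93.4% | 74% |
| 0.10 | 167 | 0.355 | 95.5% | 78% |
| 0.20 | 188 | 0.335 | 97.2% | 83% |
| 0.30 | 214 | 0.313 | 98.5% | 87% |
| 0.50 | 300 | 0.265 | 99.8% | 96% |

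The 0.3 SD column is shown because the Protocol itself expects a small effect.

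**Chance imbalance.** The difference between arms in a standardised baseline score has SE 0.1155, so its 95% range is ±1.96 × 0.1155 = ±0.226 SD. An imbalance at that limit moves the unadjusted estimate by √R² × 0.226, which is 0.07 SD at R² = 0.10 and 0.16 SD at R² = 0.50. In samples with that much imbalance:

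- the type I error of the unadjusted test is about 8% (R² = 0.10) to 21% (R² = 0.50);
- if the imbalance is adverse, power for 0.4 SD is about 82% to 57%.

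These are conditional figures at the edge of the range. Over all randomisations the error rate stays at 5%.

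**Imbalance in single factors.** For a yes/no factor with prevalence p, the SE of the difference is √(2p(1 − p)/150). At p = 0.5 this is 0.058, and a gap of more than 10 percentage points has probability 8.3%. At p = 0.2 the SE is 0.046 and the probability is about 3%. If the five factors were independent, the chance that at least one shows such a gap is 1 − (1 − 0.083)⁵ = 35% at p = 0.5, and about 14% at p = 0.2. Prevalences are not given, and independence is doubtful because arm lift, walking and verbal response all reflect severity. The 35% is therefore near a worst case.

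**Binary and ordinal outcomes.** The formulas above do not carry over to death or Rankin above 3, to mortality, or to the ordinal Rankin score. Adjustment in a logistic or proportional-odds model changes the target to a conditional odds ratio. It raises power but does not shrink the standard error by √(1 − R²). No size is claimed for these outcomes.

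**The case against.** The strongest reply is that the Protocol never says the tests will be unadjusted. Appropriate parametric tests could include analysis of covariance or logistic regression, and the choice of covariates is often left to an analysis plan, which is not at hand. This stands in part. A reader might infer that the Protocol prescribes unadjusted tests, but its wording does not go that far: it plans no adjustment and rules none out. What remains is that the Protocol does state a method, the natural reading of that method is two-group tests, and it commits to comparing groups by test at baseline.

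A reader might also infer that the trial would be biased or that its error rate would be inflated. Neither follows. The unadjusted randomised comparison is unbiased on average, keeps its 5% error overall, and has about 93% power for the stated effect. Adjustment here improves efficiency and does not repair an invalid test.

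A further inference would be that the baseline tests are meant to decide which covariates enter the model. The Protocol describes no such step.

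Finally, this is a pilot that concedes it may be too small to answer its question. It gives a reason for rejecting minimisation and a reason for recording the factors. Those choices are defensible. They do not explain leaving the factors out of the analysis, and a pilot whose estimate is a planning input has particular need of precision.

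**Conclusion.** The point holds as a worthwhile improvement to the stated method. The Protocol names only parametric and non-parametric tests and plans no use of the baseline SSS or the five factors in the treatment comparison, after simple unstratified randomisation.

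For continuous outcomes the gain ranges from modest (about 167 equivalent patients per arm, detectable effect 0.355 SD) to large (about 300 per arm, 0.265 SD). It rests wholly on the assumed R² of 0.10 to 0.50. The clearest case is the week-1 SSS, whose own baseline value is collected. For binary and ordinal outcomes a gain in power is expected but not quantified.

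**What to change.** Prespecify as the main comparison a regression on treatment, baseline SSS total and the five factors from Step 3 of the Randomisation Form:

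- week-1 SSS: analysis of covariance;
- Nottingham EADL: linear regression;
- death or Rankin above 3, and mortality: logistic regression;
- Rankin score: an ordinal model with death as the worst grade.

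Report the unadjusted result beside each. Remove significance tests at baseline and show baseline characteristics by arm descriptively.

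The cost is one paragraph and slightly more analysis work, since every covariate is already collected. The odds ratios for the binary and ordinal outcomes become conditional on the covariates. They should be labelled as such, and the unadjusted figures kept available for planning the main trial.
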